##### Activities of daily living

2.6.3.2

Activities of daily living will be assessed using the revised Chinese ADL scale (43). The scale comprises two domains: basic ADL and instrumental ADL. The former includes eating, dressing/undressing, personal hygiene, getting in/out of bed and sitting/standing, walking indoors, using the toilet, urinary/fecal control, and bathing. The latter encompasses riding public transportation, outdoor activities, cooking for oneself, taking medication on time, light housework, heavy housework, washing one’s own clothes, cutting toenails, shopping, using the telephone, managing personal finances, and staying home alone for a day. Each item offers four response options: “Can do completely independently,” “Can do with some difficulty,” “Needs assistance,” and “Cannot do at all,” corresponding to scores of 1, 2, 3, and 4, respectively. The total score ranges from 20 to 80 points, with 20–25 points indicating normal daily living abilities and 26 points or higher demonstrating impaired daily living ability (44).

##### Cognitive executive functions

2.6.3.3

Working memory will be assessed using the Digit Span Test (DST) (45). Participants will be asked to repeat sequences of digits in forward and in reverse order, with the longest correctly repeated span recorded separately for each condition. All neuropsychological tests will be administered by the same trained graduate student using standardized procedures.

Inhibitory control will be assessed using the Stroop Color Word Test (SCWT) (46). The test comprises three sets of cards, each containing 50 stimuli: (a) Chinese characters denoting colours printed in black ink; (b) coloured circles in red, yellow, blue, or green; and (c) Chinese colour words printed in incongruent ink colours. Participants will be instructed to name the character, the colour of the circle, and the ink colour of the printed word, respectively. The time required to complete each card and the number of correct responses will be recorded.

Cognitive flexibility and processing speed will be assessed using the Trail Making Test (TMT) (47). Participants will connect the dots on TMT Card A in numerical order from 1 to 25, and on TMT Card B in alternating order between numbers and Chinese characters. Time to completion will be recorded for each card.

##### Emotional state

2.6.3.4

Anxiety symptoms will be assessed using the Beck Anxiety Inventory (BAI), a 21-item self-report scale on which higher total scores indicate greater anxiety severity (48). It assesses anxiety symptoms over the preceding 7 days. The standard interpretation defines scores of 0–7 as minimal, 8–15 as mild, 16–25 as moderate, and 26–63 as severe anxiety.

Depressive symptoms will be assessed using the Beck Depression Inventory (BDI), originally developed by Beck based on the diagnostic criteria listed in the Diagnostic and Statistical Manual of Mental Disorders (4th Ed.) (DSM-IV) (49). The BDI comprises 21 self-report items rated for the preceding 7 days; higher total scores indicate greater depression severity (0–13 minimal, 14–19 mild, 20–28 moderate, and 29–63 severe).

##### Daytime functioning

2.6.3.5

Daytime fatigue will be assessed using the Fatigue Severity Scale (FSS), a 9-item self-report instrument originally developed by Krupp et al. (50). Each item is rated on a 7-point Likert scale, and the total score is calculated as the mean of all nine items, with higher scores indicating greater fatigue. A mean FSS score ≥ 4 is commonly used to identify clinically significant fatigue.

Daytime sleepiness will be assessed using the Epworth Sleepiness Scale (ESS), an 8-item self-report scale developed by Johns (51). Each item rates the likelihood of dozing in a typical daily situation (reading, watching television, sitting inactive in a public place, riding as a passenger for an hour, lying down to rest in the afternoon, sitting and talking, sitting quietly after lunch, and stopping briefly in traffic) on a scale of 0 (no chance) to 3 (high chance). The total score ranges from 0 to 24, with higher scores indicating greater daytime sleepiness.

Feasibility and acceptability outcomes will include the recruitment rate, treatment adherence (number of completed treatment sessions), retention at each follow-up visit, completion of outcome assessments, reasons for withdrawal, use of prohibited or rescue sleep-related treatments, and participant blinding responses. To address potential cultural expectancy effects, treatment credibility and outcome expectancy will be assessed after the first treatment session and after the final treatment session using the Credibility Expectancy Questionnaire (CEQ) (52); between-group differences in CEQ scores will be reported descriptively to evaluate the comparability of expectations between the acupuncture and sham-acupuncture groups. Adverse events and serious adverse events will be analyzed as safety outcomes.

#### Exploratory measures

2.6.4

Resting-state EEG will be recorded at baseline and at week 4 using the international 10–20 electrode system. Cz will serve as the reference electrode, with a sampling rate of 1,000 Hz and an online high-pass filter of 0.5 Hz. Five complementary analytic approaches will be used to extract resting-state EEG features: power spectral density, frontal alpha asymmetry, non-linear neurodynamics, functional connectivity, and EEG microstate analysis. As exploratory mechanistic hypotheses, we will test whether acupuncture compared with sham is associated with (i) reductions in relative beta power and increases in relative alpha/theta power over fronto-central regions at rest, (ii) reduced frontal alpha asymmetry, and (iii) altered contributions of microstates C and D, which have been linked to attentional and arousal networks. All EEG analyses will be exploratory, will be reported with effect sizes and 95% confidence intervals, and will be corrected for multiple testing using the false-discovery-rate procedure.

#### Measurement-instrument rationale

2.6.5

Patient-reported outcomes were selected with reference to the COSMIN framework, with attention to content validity, construct validity, reliability, responsiveness, and evidence for use in the intended population (53). COSMIN is applied here as a framework for evaluating and selecting measurement instruments rather than as a claim that the present trial independently validates these scales. The PSQI and ISI serve as the principal sleep-related patient-reported outcomes, while the BAI, BDI, FSS, and ESS serve as secondary patient-reported outcomes. The MoCA-B and MMSE are clinician-administered cognitive screening instruments and are justified separately on the basis of prior validation in Chinese and low-education populations.

#### Safety assessments

2.6.6

Liver and kidney function will be assessed during screening and after treatment to monitor systemic safety. All adverse events (AEs) occurring from the signing of informed consent to the final follow-up visit will be prospectively recorded on a standardized AE form. The form will document the type of event, onset time, duration, severity, seriousness, relationship to the intervention, management, action taken, and outcome.

Prespecified acupuncture-related AEs include needle fainting or vasovagal symptoms, pain, needle retention, subcutaneous bleeding, hematoma, local infection, metal allergy, and any other procedure-related incident requiring medical attention. Severity will be graded using CTCAE version 5.0 when applicable: Grade 1 (mild), Grade 2 (moderate), Grade 3 (severe), Grade 4 (life-threatening), and Grade 5 (death). Causality will be categorized as definitely related, probably related, possibly related, probably unrelated, or unrelated to acupuncture.

The treating acupuncturist will report AEs immediately to the study coordinator. An independent safety monitor who is not involved in treatment or outcome assessment will review AE reports regularly. Serious adverse events (SAEs), including death, life-threatening events, hospitalization or prolonged hospitalization, persistent or significant disability, or other medically important events, will be reported to the principal investigator and the ethics committee within 24 h. Treatment discontinuation criteria include participant request, Grade 3 or higher AE judged probably or definitely related to acupuncture, SAE judged related to the intervention, serious intercurrent illness, pregnancy, or substantial protocol violation. If two or more intervention-related SAEs occur, recruitment and treatment will be suspended pending safety review. All participants who receive at least one intervention session will be included in the Safety Set.

### Sample size

2.7

The sample size was calculated for the revised primary endpoint: the between-group difference in change in PSQI total score from baseline to post-treatment (week 4). In a previous sham-controlled acupuncture trial in chronic insomnia (54), sham acupuncture reduced the PSQI score to 14.76 ± 3.35 in insomnia patients post-treatment, with a sample standard deviation of s = 3.35. This study hypothesizes that acupuncture treatment for insomnia with MCI will yield an additional 2.70-point reduction in PSQI scores compared to sham acupuncture. Referencing the sample size estimation formula for two-sample mean comparisons in Medical Statistics (55), the calculation is as follows:

$$n=2{\left[\frac{\left(u_{\alpha }+u_{\beta }\right)}{\delta /\sigma }\right]}^{2}+\frac{1}{4}{u_{\alpha }}^{2}$$

A two-sided alpha of 0.05 and 90% power were used, with u0.05/2 = 1.96 and u0.1 = 1.282. This calculation yields n ≈ 33.32 per group, rounded up to 34. The standardised effect size δ/σ ≈ 0.81 corresponds to a large effect (Cohen’s d). Allowing for approximately 17% attrition, the final target sample size is 41 participants per group, for a total of 82 participants.

### Randomization and blinding

2.8

An independent statistician who will not be involved in recruitment, treatment, or outcome assessment will generate the allocation sequence using SPSS version 25.0. A computer-generated 1:1 randomization sequence will be used to assign 82 participants to the acupuncture group or the sham-acupuncture group. The allocation sequence will be concealed in sequentially numbered, opaque, sealed envelopes prepared by a researcher independent of recruitment and intervention delivery. After written informed consent and completion of baseline assessment, the next envelope in sequence will be opened by the acupuncturist to determine the assigned intervention.

This trial is participant- and assessor-blinded; acupuncturists cannot be blinded because they deliver the intervention. Participant blinding will be supported by using the same acupoint locations, number of sessions, session duration, treatment environment, fixation procedures, and standardized communication in both groups. Outcome assessors and data analysts will remain blinded to group allocation and will be physically separated from the treatment area. Participants will be reminded before each assessment not to reveal treatment sensations or perceived group assignment.

The success of participant blinding will be evaluated after the final treatment session and at the final follow-up by asking participants to guess their allocation (acupuncture, sham acupuncture, or uncertain) and to rate confidence in the guess. Blinding will be summarized using the Bang blinding index and/or James blinding index. Any accidental unblinding will be documented within 24 h, including the source, timing, personnel involved, and potential effect on outcome assessment. Participants who are unblinded will remain in follow-up and in the full analysis set; if the number of unblinded participants is meaningful, sensitivity analyses excluding them will be performed. Emergency unblinding will be permitted only when knowledge of allocation is necessary for clinical management of an SAE.

### Data collection and management

2.9

Data will be collected at baseline (within one week before the first intervention), immediately after treatment completion (week 4), at the 1-week follow-up (week 5), and at the 1-month follow-up (week 8–9). Trained outcome assessors blinded to group allocation will administer questionnaires and neuropsychological tests. Participants will complete self-report scales at the research site under standardized instructions, and a trained staff member will be available to answer procedural questions without discussing treatment allocation. Sleep diaries will be completed at home under physician guidance.

Data will be entered by trained research staff using prespecified coding rules and stored in password-protected files on a secure institutional server with restricted access. Personally identifiable information will be accessible only to essential study personnel and will be stored separately from research data. Data quality checks will be performed regularly. Participants may withdraw at any time; if a participant withdraws, the clinician will ask whether the participant is willing to complete final outcome and safety assessments, and the date and reason for withdrawal will be recorded. Protocol deviations, adherence, missing data, and use of prohibited treatments will be documented. The technical appendix, statistical code, and de-identified dataset will be available from the corresponding author upon reasonable request after completion of the study and publication of the primary results.

### Statistics and analysis

2.10

The primary analysis will use the full analysis set, consistent with a modified intention-to-treat principle. The per-protocol set (PPS) will include participants without major protocol deviations and with adequate treatment adherence. Major protocol deviations precluding PPS inclusion include violation of enrolment criteria, use of prohibited concomitant treatments (sedative-hypnotics, CBT-I, or additional acupuncture for insomnia or MCI), missing the primary endpoint assessment by more than 7 days, and completion of fewer than 8 of the 10 planned treatment sessions. The Safety Set will include all participants who receive at least one intervention session.

The prespecified primary contrast is the between-group difference in change in PSQI total score from baseline to week 4. A repeated-measures linear mixed-effects model will be used for the primary endpoint. Fixed effects will include treatment group, visit, treatment-by-visit interaction, and the baseline PSQI value; participant will be included as a random effect. An unstructured covariance matrix will be attempted first. If convergence is unstable, alternative covariance structures, including autoregressive and compound-symmetry structures, will be compared using the Akaike information criterion.

The same mixed-effects framework will be used for longitudinal continuous key secondary outcomes (ISI, MoCA-B, and MMSE) and other continuous secondary outcomes when repeated measures are available. Outcomes assessed only at baseline and week 4 will be analyzed using analysis of covariance or linear mixed-effects models adjusted for baseline value. If model assumptions are materially violated, transformations, robust estimates, or rank-based/non-parametric analyses will be used as sensitivity analyses. Categorical outcomes will be summarized as frequencies and percentages and compared using chi-square or Fisher exact tests as appropriate. CEQ scores will be summarized descriptively and compared between groups to evaluate the comparability of treatment credibility and expectancy.

Missing outcome data in the primary analysis will be handled by likelihood-based estimation under the missing-at-random assumption. Multiple imputation by chained equations will be used as a sensitivity analysis for the primary endpoint. Participants with major protocol deviations or accidental unblinding will remain in the FAS, while PPS and sensitivity analyses will assess the robustness of the findings.

Because only one primary endpoint is prespecified, no multiplicity adjustment is required for the primary hypothesis. Secondary outcomes will be interpreted as supportive and will be adjusted within clinically related domains using the Holm procedure where appropriate. Exploratory EEG analyses will report effect sizes and 95% confidence intervals; false-discovery-rate control will be applied when multiple EEG features are tested. Two-sided tests will be used, with *p* < 0.05 considered statistically significant for the primary analysis. Prespecified exploratory subgroup analyses for the primary endpoint will include age (< 65 vs. ≥ 65 years), baseline ISI severity (moderate 15–21 vs. severe ≥ 22), and educational level (≤ 6 vs. ≥ 7 years), reported as treatment-by-subgroup interaction terms and visualised with forest plots; all subgroup analyses are explicitly exploratory and hypothesis-generating. Statistical analyses will be conducted using the SPSS MIXED procedure (version 25.0) or equivalent validated statistical software (e.g., R lme4/nlme, SAS PROC MIXED).

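### No named analysis of the primary endpoint varies the missing-at-random assumption: the one missing-data sensitivity analysis, chained-equations imputation, by default repeats it

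*Protocol article*

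**What the plan says.** Section 2.10 (Statistics and analysis) of the protocol article states the assumption of the primary analysis: "Missing outcome data in the primary analysis will be handled by likelihood-based estimation under the missing-at-random assumption". The next sentence gives the only sensitivity analysis directed at missing data: "Multiple imputation by chained equations will be used as a sensitivity analysis for the primary endpoint". It states no shift of imputed values, no imputation from the reference arm and no tipping-point search.

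Three other robustness checks are named:

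- **Deviations and unblinding (2.10):** "Participants with major protocol deviations or accidental unblinding will remain in the FAS, while PPS and sensitivity analyses will assess the robustness of the findings".
- **Unblinding (2.8):** "if the number of unblinded participants is meaningful, sensitivity analyses excluding them will be performed".
- **Model assumptions (2.10):** "transformations, robust estimates, or rank-based/non-parametric analyses will be used as sensitivity analyses".

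Three further facts bear on the point. Section 2.7 sets the size of the trial with an allowance for loss: "Allowing for approximately 17% attrition, the final target sample size is 41 participants per group, for a total of 82 participants". Table 1 and section 2.6.1 place PSQI at baseline and at weeks 4, 5 and 8–9, so there is no PSQI between baseline and the primary time point. Under section 2.9, people who withdraw are asked whether they will still complete the final assessments, and the date of and reason for withdrawal are recorded.

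**The concern.** A sensitivity analysis for missing data is informative to the extent that it changes what is assumed about the unseen values. Likelihood estimation in a mixed model and ordinary chained-equations imputation both assume that, given the variables in the model, missing and observed participants have the same outcome distribution. If both use the same variables, they aim at the same estimate. Their agreement would then say nothing about what happens if participants with missing data did worse, or better, than MAR implies.

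The assessment schedule makes this matter. Someone who leaves during treatment and declines later assessment has no PSQI after baseline. For that person the stated primary model relies on baseline PSQI and arm alone. MAR then amounts to assuming that they fared as well as completers in the same arm with the same baseline score. Departures could differ by arm, because only the acupuncture arm has skin penetration and manipulation (section 2.5).

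At stake is whether a reader of the results can tell a solid finding from a fragile one.

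**Working it through.** **1. Which analysis varies the missing-data assumption?**

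| Analysis | What it varies | Varies MAR? |
|---|---|---|
| Primary mixed model (2.10) | – | Assumes MAR |
| Chained-equations imputation (2.10) | Estimation route, and possibly the conditioning variables | No, unless an adjustment is added; none is stated |
| Per-protocol set (2.10) | Who is included, by deviation and adherence | No |
| Excluding unblinded participants (2.8) | Who is included, by blinding | No |
| Transformations, robust or rank-based methods (2.10) | Distributional assumptions | No |

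**2. The plan's own figures (section 2.7).** Inputs: difference 2.70, SD 3.35, two-sided alpha 0.05 (1.96), 90% power (1.282).

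- n = 2 × [(1.96 + 1.282)/(2.70/3.35)]² + 1.96²/4 = 32.36 + 0.96 = 33.32, rounded up to 34 per group.
- 34/0.83 = 40.96, rounded up to 41 per group, 82 in total.
- Implied loss: 7/41 = 17.1% per group.

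The stated sample size reproduces, and this point does not change it.

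**3. How far a departure from MAR moves the effect.** Assumptions, not figures from the plan: all 7 of 41 per arm are missing at week 4; missing acupuncture participants score D PSQI points worse than MAR predicts; missing sham participants follow MAR.

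Shift = (7/41) × D = 0.171 × D

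| D | Shift | Effect left from 2.70 |
|---|---|---|
| 1 | 0.17 | 2.53 |
| 2 | 0.34 | 2.36 |
| 2.7 | 0.46 | 2.24 |
| 4 | 0.68 | 2.02 |

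D = 2.7 is roughly what a reference-based run would assume if the planned effect were true, with acupuncture dropouts doing no better than sham.

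**4. Tipping point.**

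- SE = 3.35 × √(2/34) = 0.812.
- Smallest significant difference = t(0.975, 66 df) × SE = 1.997 × 0.812 = 1.62.
- Tipping D = (observed difference − 1.62)/0.171.
- Observed 2.0 (assumed): 0.38/0.171, about 2.2 points.
- Observed 2.70 (the planned effect): 1.08/0.171, about 6.3 points.

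With 1.96 in place of the t quantile the threshold is 1.59, and the two tipping points are about 2.4 and 6.5. The SE is held fixed as D changes, which is a simplification.

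**5. When the same shift applies in both arms.** The bias is (difference in missing proportions) × D.

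- 7 and 7 missing: zero at any D.
- 10 acupuncture and 4 sham missing, D = 2: (10/41 − 4/41) × 2 = 0.29 points in favour of acupuncture.
- 4 and 10 missing, D = 2: 0.29 points against it.

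**The case against.** The strongest reply is one of scope. The article is condensed, an SAP may exist, and delta shifts or reference-based runs are the kind of detail an SAP adds, often on top of chained-equations output. Nothing in section 2.10 is false, and the MAR assumption of the imputation is inferred from the method, not stated. This stands in part: absent imputation detail would be no finding. But the article does not leave the choice open. It selects the missing-data check for the primary endpoint, and the one selected by default repeats the primary assumption.

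Four other replies limit the point:

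- **Auxiliary data.** Imputation could use ISI, the sleep diary or adherence, which would change what MAR conditions on. A reader might infer that the imputation tests nothing or that any robustness statement is empty. The documents do not support that, because they do not say the variables will match those of the primary model. They name no auxiliary variables either. What the imputation leaves untested is departure from MAR.
- **Amount missing.** A reader might infer that 17% of week-4 scores will be missing. The plan says only "Allowing for approximately 17% attrition". Someone lost after week 4 still supplies the primary endpoint, and section 2.9 seeks final assessments from people who withdraw. Seven of 41 is an upper-end assumption.
- **Direction.** A reader might infer that the effect would be inflated. That does not follow. If lack of relief drives dropout and acupuncture works, more such dropout would be expected under sham, and the bias could run against acupuncture.
- **Size.** The SD of 3.35 ignores the gain from baseline adjustment. With an assumed baseline correlation of 0.5, the threshold falls to 1.62 × √0.75 = 1.40, and the tipping D for an observed 2.0 rises to about 3.5.

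These replies bear on the likely size and direction. None supplies an analysis that varies the assumption.

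**Conclusion.** The point holds as limited here: no named analysis can show whether the primary result is robust to departures from MAR. The primary analysis itself stands, and so does the sample size.

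The consequence depends on the result. Under the illustration's assumptions, a result at the planned effect would survive all but an implausibly large departure, more than twice the treatment effect itself, whereas a result near 2.0 would not survive a departure of about 2.2 points. The plan as written cannot tell these situations apart. The figures rest on the arm-specific shift, the 7 of 41 missing and the assumed observed differences. Fewer missing scores or a smaller SE would raise both tipping points.

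This is a worthwhile, cheap repair of the sensitivity analysis. It is not evidence that the trial's conclusion would be wrong.

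**What to change.** Keep the MAR imputation as it is and prespecify two additions, before unblinding:

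1. **Delta-adjusted imputation of week-4 PSQI.** Impute under MAR, then add D = 0, 1, 2, … points to the imputed values in the acupuncture arm, and in a separate set of runs to those in both arms. Report the estimate and confidence interval at each D, and the tipping point at which p exceeds 0.05.
2. **One reference-based run.** Impute acupuncture dropouts from the sham arm.

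Report the number missing at week 4 by arm beside these results, so that the tipping point can be judged against the actual loss.

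The cost is a few more imputation runs and one table. No new data are needed and the sample size does not change. The drawback is that the conclusion may look less robust.
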